## 5.0 LAY ABSTRACT

Heart attacks are common. They may be major or minor. Smaller heart attacks occur when a blood clot forms on narrowing's in the coronary arteries and then cause partial blockage of the artery supplying blood to the heart. If they are not treated appropriately then the artery may block completely which can result in poorer outcomes (such as major heart attack or death). Published Guidelines tell us that these small heart attacks need to be treated. Such patients are therefore admitted to hospital, given drugs to prevent more clot forming, and within 3-4 days, are taken to the catheter laboratory (a special X ray room) where any narrowing's in the coronary arteries can be seen on the X ray screen and treated, where necessary, with a balloon and stent (angioplasty).

We are able to detect that there has been a heart attack by the release of small amounts of protein from injured heart muscle – these proteins are known as “troponins” and they can be measured using a blood test. Recently, it has been possible to detect small amounts of troponins in the blood very early after admission in patients with small heart attacks. Hence, we are now able to determine how severe the heart attack is according to the blood levels of early measured troponins. If we put these measured levels into an app programme together with some patient details such as age and kidney function, we come up with a score that tells us what the future risk to the patient is. If the calculated score is high, this suggests it may be better to treat this type of patient much earlier with balloon and stent than is currently undertaken, although this has never been proven. Alternatively, patients may be better left for longer on the medical treatment until the balloon and stent treatment. In this study we are therefore comparing the strategy of going to the cath lab early and treating if necessary as compared with going to the cath lab according to current standard timings.

The outcomes that we will measure to test whether very early balloon and stent in higher risk patients is actually beneficial, will be: death, further heart attack or heart failure occurring over the subsequent 12 months of follow up. We will also undertake a special cardiac heart scan called an MRI to see if the heart attack is smaller with earlier balloon and stent, and measure levels of circulating proteins in the blood called biomarkers.

## 6.0 INTRODUCTION

N-STEMI ACS is a condition that results from atheromatous plaque erosion/rupture and the subsequent formation of peri-plaque embolic thrombus that is not occlusive, but may become so (and so lead to STEMI). The management of such patients involves administration of potent anti-platelet agents (P2Y12 blockers) and anti-thrombins such as low molecule weight heparin (LMWH) (1–5) in order to attenuate the formation of any evolving platelet-centric thrombus formation. The TACTICS -TIMI 18 (6), FRISC II (7) and RITA-3 (8) trials together with meta-analyses (9–11) strongly indicate that N-STEMI ACS patients benefit from in-patient coronary intervention. PCI has thus become a Guideline recommendation as part of N-STEMI ACS management (12). However, the actual timing of the PCI to provide best clinical outcomes is less clear. Whether there is a benefit from a period of several days of medical therapy that includes antiplatelet agents and high dose statins and which could theoretically result in plaque passivation and reduced clotting tendency, is a possibility that has never been prospectively and robustly tested. Although a number of studies have attempted to provide evidence for the best timing of in-hospital PCI intervention and especially whether there is any benefit in very early intervention, all are

RAPID-NSTEMI[figure not shown]

somewhat flawed. For example so-called “early” PCI in some trials was not actually early at all: in the ICTUS (13,14) and TACTICS (6) trials, “early” PCI intervention was undertaken at a median time of 23 and 24 hours respectively, and in FRISC-II and RITA-3 trials (7,8) “early” PCI was actually very late indeed (median 96hrs). Furthermore, interpretation of trial outcomes is confounded by differing trial logistics, including trial inclusion criteria. Only 3 trials (see below) assessed really early intervention – of these, one was driven by non-clinical end points and another small study showed adverse outcomes in early intervention, contrary to all other trials. Specifically, in the ABOARD study (15) patients were randomised to immediate PCI or intervention the following day, but the primary end point was enzyme-determined infarct size, not clinical outcomes. Additionally, the lack of risk stratification could account for the demonstrated lack of difference even in the non-clinical endpoint. The OPTIMA study (16) compared immediate PCI versus PCI delayed for 24-48 hours and the incidence of 6 month primary end point (death, non-fatal MI, unplanned revascularisation) was significantly higher in the early group (intervention at median 25 minutes from randomisation) compared to those in the delayed (25 hour) group (RR=1.5, 95% CI=1.10-2.07, p=0.008). This small study (n=140) suggests a case could be made for so-called “pharmacological passivation” prior to PCI. However, nearly all of the end-point difference occurred in the acute stages, suggesting perhaps it was acute events (i.e. PCI related events) that drove any differences. In the LIPSIA-NSTEMI-ACS study there was no significant difference between immediate (within 2hr) and early (within 24hrs) PCI in higher-risk N-STEMI ACS patients with GRACE score >140. However, again this study was not powered to detect differences in clinical events; only differences in CK-MB (17). The best study, the RIDDLE N-STEMI trial, randomised 323 N-STEMI ACS patients to receive either immediate (<2h from randomisation) or delayed (2-72hr, median time in trial 61hr) PCI (18). This relatively small trial showed 30-day primary endpoint of death or new MI was lower in the immediate PCI group (4.3% vs. 13%, HR=0.32, 95% CI=0.17-0.67, p=0.002). This difference was driven by re-infarction in the delayed PCI group while awaiting angiography. There was no difference in the composite endpoint in a landmark analysis from 31days-1yr. Again, this trial was underpowered to detect new MI post-discharge and also to detect any impact on death up to 1 year post N-STEMI ACS. As with all of the studies quoted above, GRACE score was not used as a criteria for enrolment and only 36% of the study population retrospectively had a GRACE score >140.

In a meta-analysis by Kastrati (19) no benefit in hard end points (death/AMI) as a result of early intervention was demonstrated, although there was a reduction in recurrent ischaemia within the early revascularisation group (RR=0.57, 95% CI=0.44 – 0.74, p<0.001). A more recent meta-analysis (20) of 7 RCTs (5370 patients) and 4 observational studies, showed, in the total 77,499 patients, that there was no conclusive evidence of a survival benefit from very early intervention (in the randomised studies). However, the range of “early” intervention was 0.5-14hrs, and for delayed intervention was 20–86hrs post-randomisation. A third meta-analysis suggests early routine invasive strategy appears to reduce the 5-year risk of the combined endpoint of cardiovascular death and myocardial infarction, with separate reductions in the risk of myocardial infarction and cardiovascular mortality (21).

In conclusion, the currently available data are discrepant and not of sufficient scientific quality to accurately inform the best management of this very large group of patients.

## 6.1 THE IMPACT OF THE GRACE SCORE

In a post hoc subgroup analysis of the TIMACS study, those patients who had a GRACE score of >140 were shown to benefit from early intervention with significant improvement in

RAPID-NSTEMI[figure not shown]

outcomes (HR=0.65, 95% CI=0.48-0.88,  $p=0.005$ ) (22). Hence, a larger prospective and appropriately powered trial in N-STEMI ACS patient is required to detect any real differences from very early intervention. In many studies the early intervention was not early and the delayed intervention occurred beyond the guideline recommended 72hrs. Patients have not been stratified as higher risk by GRACE score and trial numbers have not allowed for assessment of any strategy on clinical end points. Currently no consensus on whether immediate PCI leads improves outcomes can be formed, due to conflicting, and contrary reporting data. The TIMACS post hoc GRACE score analysis suggests the cut off should be  $>140$  but this was GRACE score version 1.0. As such it is likely that to use this cut off will only identify those patients determined by GRACE score to be highest risk according mostly to demographics such as age. We have taken a more subtle approach using GRACE score 2.0 (APPENDIX I) to identify a higher risk population according to % event rates at 6 and 12 months.

## 6.2 SCIENTIFIC PRINCIPLES UNDERLYING THE PROPOSED RESEARCH

Clinical presentation and outcomes of N-STEMI ACS reflect a process of incomplete occlusion of the coronary artery by platelet aggregation and thrombus formation at the site of an eroded/ruptured atherosclerotic plaque. While intuitively the case could be made for immediate PCI to prevent complete occlusion by establishing optimal flow (in accordance with Virchow's principle) it can be argued that the use of anti-platelet and anti-coagulant agents, as well as high dose statins, for a period of time could be beneficial. This should theoretically allow any disrupted plaque to become stabilised, so promoting autolysis, and hence attenuate the presence of clot and so reduce risk of PCI induced embolisation at early PCI (Type 4a MI). Delay to allow for so-called passivation may also reduce the risk of true "no reflow" phenomenon, and decrease risk of microvascular obstruction. On the other hand, the recent introduction of more potent  $P_2Y_{12}$  inhibitors (Ticagrelor or Prasugrel) will lead to earlier and more effective platelet inhibition over a shorter time period prior to early PCI, perhaps negating the need for a period of time to passivate the vessel wall.

Earlier identification of higher risk N-STEMI ACS patients is now possible through the introduction of Hs-Troponins, which allow early assessment of degree of myocardial injury and so patient risk, and thereby allow for earlier decisions around use of an interventional strategy.

The RAPID-NSTEMI trial, which utilizes these principles, has been designed to determine whether early risk assessment and early intervention improves outcome. This study would aim to provide a robust definitive answer to the question whether immediate revascularisation in higher risk N-STEMI patients confers benefit.

## 6.3 JUSTIFICATION FOR THE STUDY

All trials on timing of intervention in N-STEMI ACS to date have varied in their statistical design, choice of end points and patient inclusion criteria, and some also appear methodologically flawed, for e.g. in ISAR-COOL a different definition of MI was applied to the two trial groups. All trials testing so-called true very early intervention have been under-powered for clinical outcomes. In addition, randomisation in most trials was undertaken following measurement of standard troponins, introducing an inevitable delay before randomisation could take place, limiting their ability to robustly test true "early" intervention. The question therefore remains open, making RAPID-NSTEMI a novel study. Contemporary Hs-Troponins allow detection of N-STEMI within 1-2 hrs of admission as opposed to the 8-12hrs for standard Troponins, thus allowing earlier identification of the

RAPID-NSTEMI[figure not shown]

higher risk N-STEMI ACS patients (23,24). The diagnostic sensitivity of a two hour rule-in protocol for ACS using Hs-Troponin-I was demonstrated to be in the range 95%-97% with specificity ranging between 78%-82% (25,26) used Hs-Troponin-T and demonstrated sensitivity of 96%-99% with a positive predictive values of 78%-85%.

If the immediate admission Hs-Troponin is raised above the normal range for that hospital, then the GRACE score 2.0 will be calculated at that point. We will know within 2-3 hours post-admission (accounting for 1hr for the result to become available) which of the patients has a GRACE score that allows them to be deemed "higher risk" and so included in the study. We believe use of the GRACE score is justified (>300 publications, >20,000 patients), and this is consistent with current NICE guidelines for risk stratification of ACS patients. We will use the adapted GRACE 2.0 score (where there is no need for knowledge of the creatinine or Killip grade). We have debated at length the value of the score cut-off and believe the following to be correct for the potential beneficial impact of very early intervention in N-STEMI patients – **Inclusion criteria = GRACE-2 score  $\geq 118$ , or  $\geq 90$  with additional high risk features.** These levels are based on in depth review of the GRACE 2.0 score outcomes and the desire to impact sufficient numbers of N-STEMI ACS patients.

We will randomise these higher risk patients at an early time point to immediate angiography with a view to follow-on revascularisation (i.e. go to the cath lab ASAP with no additional avoidable delay – so-called "STEMI-like treatment") or to revascularisation according to standard care – intervention preferably within 72 hours as per ESC Guidelines. <https://www.escardio.org/Guidelines/Clinical-Practice-Guidelines>  
Irrespective of result RAPID-NSTEMI will focus clinicians on need for early evaluation and assessment of patients presenting with ACS to determine which patients should be managed earlier.

#### 6.4 EXPECTED VALUE OF RESULTS

RAPID-NSTEMI will answer an important clinical question: can outcomes in higher risk N-STEMI ACS patients be improved with immediate PCI in higher risk populations, compared to current standard care? This trial will inform clinical practice and International Guideline Committees, regardless of the result. We may be able to rationalise the ACS service and determine the impact of any results on service provision and so redirect clinician's focus on risk assessment. For example, whilst cardiac networks exist for primary-PCI for STEMI, given the incidence of N-STEMI ACS, such networks may need to be enhanced if clinical benefit were demonstrated with this study. This balance between determining what is best for patients, and potentially over burdening already stretched ACS networks will be a vital consideration but can only be resolved if studies such as RAPID-NSTEMI suggest significant clinical benefit, or not. This question as to best timing of intervention, be it immediate or as current, somewhat delayed (see BCIS data below) is unanswered. Relative to their numbers and important clinical outcomes, N-STEMI ACS patients are an under-studied group.

#### 6.5 HYPOTHESIS TO BE TESTED

RAPID-NSTEMI will test the following hypothesis:

Immediate angiography with a view to follow on revascularisation in patients presenting with N-STEMI ACS and at higher risk (GRACE score  $\geq 118$  or  $\geq 90$  with additional high risk features), will result in a significant reduction in rate of major adverse clinical outcomes

RAPID-NSTEMI[figure not shown]

(death/MI/hospitalisation for heart failure) within 12 months compared with angiography with follow on revascularisation undertaken according to current standard of care.

Randomisation will take place prior to angiography, following GRACE 2.0 score assessment. At angiography it will become clear that a percentage of patients will require CABG (~8%), some will have normal coronary arteries and some will be treated medically but the analysis will be on an intention to treat (ITT) basis, since randomisation needs for logistical reasons to be undertaken prior to angiography. While the final analysis will be ITT, outcomes according to actual treatment received will also be reported separately as a “per treatment received” analysis.

This will be very important since it will test the hypothesis as to whether very early received intervention is better than current standard of care. Thus, a secondary analysis will be those who receive revascularisation at the time of very early angiography versus those who receive revascularisation at the timing of current standard of care.

We expect this to be a Guideline-informing, clinical practice-directing trial that will help direct clinicians as to the timing of PCI in N-STEMI ACS patients. The trial is didactic, simple, robust, and will be managed by experienced interventional trialists and a registered Clinical Trials Unit, all with a track record for trial delivery.

RAPID-NSTEMI[figure not shown]

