The primary outcome for the main study will be a 12-month composite of Major Adverse Cardiovascular Events (MACE) consisting: overall mortality/new MI/admission with heart failure.

Power calculations indicate that 2314 patients are required to show MACE superiority for early intervention in such higher risk N-STEMI ACS patients.

Analyses will be primarily according to “intention to treat”, with a secondary analysis according to trial treatment received (comparing those who actually received follow-on revascularisation at the two different trial time points). There will be a cost effectiveness analysis.

We will undertake a mechanistic CMR sub-study and biomarkers sub-study in the two groups. Expected value of results: We have designed a superiority trial to anticipate that the outcomes will be improved in higher risk patients revascularised very early after presentation. Irrespective of outcome, this trial should determine whether there is a need for a change in current patient management of a common condition and in particular if all N-STEMI patients should be admitted to a PCI-capable hospital to allow for very early intervention. The results will inform National/International Guidelines, and guide healthcare

RAPID-NSTEMI[figure not shown]

service provision. The planned cost effectiveness analysis will become particularly important if clinical outcomes are no different between groups since length of stay should be different.

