- recurrent dynamic ECG changes
- haemodynamic instability during the wait till angiography

will be allowed to cross to earlier angiography +/- revascularisation as per best clinical practice. Reasons for cross-over will be carefully documented. Crossover rates will be carefully monitored for accuracy but if crossover occurs, this will be measured as a secondary end-point.

We have considered carefully whether this design will allow sufficient temporal separation between the two groups enabling robust interpretation of the results. According to the 2015 BCIS audit returns, the median time to angiography for patients (directly) admitted to a PCI-capable centre with N-STEMI ACS = 60.8 hours, and for inter-hospital transfer = 82.1 hrs. Apart for one outlier the earliest time for the direct admission patients appears to be in the order of 26 hours. The risk of time contamination between groups A and B will be minimised by strict trial discipline; without this discipline the study will be difficult to interpret and will not be robust. The “times to intervention” will be important trial audit measures. All recruiting sites will be asked to treat the standard care arm participants according to their

RAPID-NSTEMI[figure not shown]

NHS Trust's current practice. To reduce time delay in Group A only trial sites with on-site cath labs will be included.

All patients will be included in a within-trial cost effectiveness analysis.

A mechanistic CMR sub-study of 200 patients (100 from each group) will evaluate LV function, and differences in infarct size (especially the impact of Type 4a MIs) between groups (APPENDIX V).

A biomarkers substudy will investigate if novel biomarkers can predict the need for PCI and future clinical outcomes (APPENDIX VI)

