**7.7 RANDOMISATION**

Randomisation will be performed by the research nurse/enrolling physician using a validated Interactive Voice Response (IVR) or Interactive Web Response (IWR) System ("Sealed Envelope Ltd") provided through the LCTU. Eligible participants will be randomly assigned in a 1:1 ratio to one of two arms:

- GROUP A: Immediate angiography with follow-on revascularisation if indicated  
or  
GROUP B: Standard angiography with follow on revascularisation if indicated, - within Guideline recommended times.  
Standard interim therapy such as LMWH/DAPT will be mandated in this group until angiography.

Randomisation will be stratified by hospital site, with minimisation within each hospital site strata for the Grace score category. Due to the nature of the intervention, blinding of the participants or the study team to the randomisation arm is not possible.

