8.0 STATISTICAL ASPECTS

8.1 Power calculations

The power calculations are based on the results of several studies including the retrospective TIMACS study (11,22). Subsequently a post-hoc analysis using GRACE score was applied - patients with a GRACE risk score of >140 (equating to the third with the highest risk) in the early-intervention group had a primary outcome 13.9%, and in the delayed group of 21.0%, a reduction of 35% at 6 months. (HR=0.65; 95% CI, 0.48-0.89; P=0.006). We have decided to include admission for heart failure since there is clear evidence that this is an important outcome following admission with N-STEMI ACS (27) with rates between 5.6% (28) and 15% (29). The best data on new heart failure comes from Kaul (30) who reported a 12.8% incidence.

We have also calculated outcomes based on imputing data into the GRACE score 2.0 and on review of all data, concluded that a GRACE 2.0 score of ≥118 or ≥90 with further high risk clinical factors provides similar outcomes to the proposed event rates. Those with the intermediate GRACE 2.0 risk score (i.e. ≥90) are included providing they have one other high risk features not captured by GRACE 2.0 namely anterior “infarction”, ST segment depression, diabetes (on medication) and a Hs Troponin rise > 3x ULN.

Both the GRACE 2.0 of ≥118 or the GRACE 2.0 ≥90 with one of the risk factors, together with the heart failure data, will provide patient with an event rate ~19%.

Since outcomes have improved somewhat over recent times we have powered RAPID-NSTEMI conservatively to detect a 25% reduction in the composite primary end point.

Standard intervention arm (Group B), predicted primary outcome events = 19%.

Immediate Intervention arm (Group A) predicted primary outcome events = 14.25% (odds ratio of 0.71, relative risk reduction of 25%).

|                                       |        |
|---------------------------------------|--------|
| Effect size (relative risk reduction) | 25%    |
| MACE rate standard PCI group          | 19%    |
| MACE rate Immediate PCI group         | 14.25% |
| Number of patients per group          | 964    |
| Total number of patients in study     | 1928   |
| Total number including 5% drop out    | 2314   |
| 5% crossover and 8% CABG treatment.   |        |

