To achieve a power (1-β) of 80% with a (two sided) α=0.05, 964 patients are required in each arm. Assuming up to 5% drop-outs, 5% crossover, 8% needing CABG 1157 patients will be recruited to each of the treatment arms A and B, leading to a total of 2314 patients. (Risks to complete recruitment **APPENDIX VI**).

Based on the above, we consider the power calculations to be conservatively robust and the proposed sample size of sufficient power to detect a significant (and clinically important) reduction in primary endpoint. The calculations have been performed in STATA v14 using the  $\chi^2$  test of equal proportions with the support of the proposed trial statistician.

The trial will follow an adaptive design with closed DSMC review of standard of care event rates.

RAPID-NSTEMI[figure not shown]**8.2 STATISTICAL ANALYSIS PLAN**

Statistical analyses will be undertaken according to a pre-trial Statistical Analysis Plan (SAP) which will be prepared by the statistician employed on the study. Descriptive characteristics at baseline will be presented by treatment arm.

The Primary endpoint is composite outcome of major cardiovascular events (MACE–Death/MI/admission with heart failure) within 12 months, and secondary analyses will be performed for MACE at 30 days following identical methodology. All analyses will be performed following the intention-to-treat principle, with subsequent “immediate follow-on revascularisation” secondary analyses. The primary analysis will investigate the proportion of participants having a primary outcome in each arm, with OR and 95% confidence interval calculation. Additional analyses will compare events in Group A and B with a “time-to-event” endpoint of the primary outcome occurring up until 12 months. Two-sided 95% confidence intervals will be presented for the primary endpoint and all secondary end-point comparisons between groups. The detailed statistical analysis plan will be produced and agreed with the Trial Steering Committee, Sponsors and trial funders prior to trial initiation. The trial will be registered with [clinicaltrials.gov](https://clinicaltrials.gov).

A methods paper outlining the trial will be sent to an appropriate recognised journal for publication.

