## APPENDIX VII Risks to recruitment

### Compliance and loss to follow-up.

The main risk to completing this trial and its robust interpretation will be inappropriately delayed PCI in the very early group and/or early over enthusiastic intervention in the standard arm group with “time contamination”. Study discipline is essential.

Other risks include loss to follow-up and patient withdrawal from the study. We have accounted for a potential loss-to-follow-up rate of 5% in our power calculations. The sample also includes those who randomised to standard treatment require urgent intervention (ie crossovers). In addition, some patients may be referred for CABG instead of undergoing PCI if there is evidence of complex lesion anatomy or multi-vessel disease with high SYNTAX score. Again, we estimate from the ABOARD study that this should be ~8% of patients. Furthermore some (a few %) will have normal coronary arteries and others will need to be treated medically (diffuse disease). While all patients randomised to the study will be analysed with “intention to treat” analysis, there will also be a subsequent analysis according to the actual hypothesis being testing: comparing trial treatment received (very early intervention with delayed/standard intervention).

Regarding the recruitment risk to the project, there is always a potential risk of lack of up-take or slow recruitment rate from the participating sites. Thus, we will arrange for 3 regional study-related investigator meetings (Glasgow, Southampton and Oxford) to which 2 members of each centre (PI and research nurse) will be invited to go over trial logistics and recruitment. The clinical research fellow employed for the study will be the important co-ordinator and will work closely with the trial manager to provide regular updates on recruitment rates to participating sites to encourage recruitment. The use of a per-patient recruitment fee should also encourage recruitment to the study by participating sites. This is a portfolio study so will have NIHR funded nurse support.

We will be initiating recruitment in 5 large sites to give the trial a positive kick start.

[figure not shown]

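### The treatment-received comparison selects patients after randomisation and is biased, yet the protocol says it tests the trial hypothesis

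*Protocol*

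**What the plan says.** Section 6.5 states the hypothesis as a strategy: immediate angiography, with a view to revascularisation, reduces 12-month death, MI or heart-failure admission in higher-risk patients compared with standard timing. It says the final analysis will be ITT because randomisation precedes angiography. It then adds a comparison by treatment actually received, calls it very important because it tests whether early received intervention is better than standard care, and defines it: "a secondary analysis will be those who receive revascularisation at the time of very early angiography versus those who receive revascularisation" at the timing of standard care.

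The same comparison appears elsewhere:
- Section 4.0 plans ITT first, "with a secondary analysis according to trial treatment received", restricted to patients actually revascularised.
- Section 8.2 adds secondary analyses of immediate follow-on revascularisation after ITT.
- Section 8.3 repeats it as a sensitivity analysis of cost-effectiveness.
- Appendix VII, under compliance and loss to follow-up, says "there will also be a subsequent analysis according to the actual hypothesis being testing: comparing trial treatment received".

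Two other provisions decide who can be in each group. Under section 7.4, Group B patients with continuing pain, recurrent dynamic ECG changes or haemodynamic instability "will be allowed to cross to earlier angiography +/- revascularisation as per best clinical practice". Section 7.8 leaves the decision to revascularise to the operator at angiography. Section 7.2.2 collects deaths before planned angiography as an outcome.

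**The concern.** The hypothesis in 6.5 concerns all randomised patients. The comparison said to test it keeps only patients with a particular event after randomisation, so its groups are no longer the randomised ones.

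Two of the ways in which they differ come from the protocol itself. A Group B patient who dies before angiography cannot enter the standard-timing group, while the Group A counterpart, treated at once, stays in the early group. A Group B patient who deteriorates may leave standard timing because of that deterioration. Both remove higher-risk patients from the comparator.

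This comparison could therefore disagree with the ITT result for structural reasons alone. The protocol's wording would then invite readers to treat it as the better answer to the real question. Section 8.3 would carry the same distortion into the economic evaluation.

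**Working it through.** **The plan's own figure.** Section 8.1 says: "To achieve a power (1-β) of 80% with a (two sided) α=0.05, 964 patients are required in each arm". With 19% and 14.25%, n = [1.960·√(2·0.16625·0.83375) + 0.842·√(0.19·0.81 + 0.1425·0.8575)]² / 0.0475² = (1.032 + 0.442)² / 0.002256 ≈ 963.2, so 964 per arm. The odds ratio is (0.1425/0.8575)/(0.19/0.81) = 0.71. Both agree with the protocol. The protocol gives no figure for the treatment-received comparison.

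**Inputs from the protocol.** Risk p = 0.19, taken as common to both arms under no timing effect (8.1). Crossover x = 5% of Group B (8.1). Share needing PCI s = 2/3 (Appendix VI, sample size). Recruited 1157 per arm (8.1). Median wait 60.8 hours for direct admissions, from a national audit (7.4).

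**Inputs assumed, because the documents give none.** Crossover risk r times average. A proportion d of Group B patients who would have been revascularised but die before angiography. Every crossover is revascularised.

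**Early deaths alone (crossovers kept in Group B).** Delayed risk = (p − d)/(1 − d), so delayed odds = (p − d)/(1 − p) and OR = p/(p − d):
- d = 0.5%: 0.19/0.185 = 1.03
- d = 1%: 0.19/0.18 = 1.06
- d = 2%: 0.19/0.17 = 1.12

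**Crossovers moved to the early group, or dropped.**
- Early risk = p(s + xr)/(s + x) if moved, or p if dropped.
- Delayed risk = (sp − xrp − sd)/(s − x − sd).

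| r | d | Early (moved) | Delayed | OR, moved | OR, dropped |
|---|---|---|---|---|---|
| 1 | 0 | 0.190 | 0.190 | 1.00 | 1.00 |
| 1.5 | 0 | 0.197 | 0.182 | 1.10 | 1.05 |
| 1.5 | 1% | 0.197 | 0.173 | 1.17 | 1.12 |
| 2 | 0 | 0.203 | 0.175 | 1.21 | 1.11 |
| 2 | 1% | 0.203 | 0.166 | 1.29 | 1.18 |

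With s = 0.75 (PCI plus the 8% CABG), the four moved values with r above 1 run from 1.09 to 1.26. With r = 3 and s = 2/3 they would be 1.46 (d = 0) and 1.57 (d = 1%). With 1157 per arm, s = 2/3, d = 0 and crossovers moved, the chance of a significant result against early treatment is 11% (r = 1.5) or 30% (r = 2), against a nominal 2.5% under ITT.

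**If early treatment works as planned.** Keep s = 2/3, r = 2, d = 0 and put Group A at 14.25%. Early risk with crossovers moved = (0.095 + 0.019)/0.7167 = 0.159, against 0.175 delayed: OR 0.89. With crossovers dropped, 0.1425 against 0.175 gives OR 0.79. The design value is 0.71.

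**Conditions that reverse the sign under no timing effect** (crossovers moved, d = 0):
- *CABG classed out of the early group only*, because surgery does not happen at the early angiogram (s = 0.75, r = 1.5, 8% CABG). At twice average CABG risk, early = (0.1425 − 0.0304 + 0.01425)/0.72 = 0.175 and delayed = (0.1425 − 0.01425)/0.70 = 0.183: OR 0.95. At 1.5 times, OR 1.02.
- *Waiting moves 10% of Group B, at half average risk, to medical management* (s = 2/3). With r = 1.5, delayed = (0.1267 − 0.0095 − 0.01425)/0.5167 = 0.199: OR 0.98. With r = 1, OR 0.89.
- *An MI while waiting brings an extra 2% of Group B to revascularisation* (s = 2/3, r = 1.5). Delayed = (0.1124 + 0.02)/0.6367 = 0.208: OR 0.93.

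**The case against.** The strongest reply is that the comparison is subordinate. Sections 4.0 and 6.5 call it secondary, Appendix VII calls it subsequent, 8.3 treats it as sensitivity analysis after ITT, and no alpha, power or decision rule attaches to it. That stands: a reader might infer that the trial's confirmatory conclusion is at risk, and the documents do not support this. It does not excuse the wording. A secondary label does not cure a statement that the comparison tests the hypothesis.

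A reader might also infer that the analysis will show early revascularisation as worse whenever timing has no effect. That is too strong. The size rests on crossover risk and pre-angiography deaths, neither of which is given. Deaths of 2% would be more than a tenth of the expected 19% events (2/19), in patients screened to exclude shock and instability. The protocol does not say that crossovers join the early group. Section 7.4 speaks only of earlier angiography, and 7.2.2 counts urgent revascularisation as a Group B outcome, so they may stay in Group B. The sign can also reverse, as shown above.

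Classification rules and adjustment may be in the SAP, which is not shown, so their absence here is not itself the fault. The fault is the status the protocol gives to the comparison, which a SAP would not remove from these sections.

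Finally, one might conclude that a complier-average analysis must replace it. That goes too far. Assignment also changes angiography timing and interim drug treatment in patients never revascularised, which strains the exclusion restriction. Its control condition would also mix delayed with no revascularisation.

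**Conclusion.** The concern holds in limited form. The treatment-received comparison conditions on an event after randomisation and is biased, yet the protocol presents it as a test of a hypothesis that it defines for all randomised patients. Its crossover and early-death mechanisms tend to disfavour early revascularisation. Under no timing effect the odds ratio is about 1.03 to 1.12 from early deaths of 0.5% to 2% alone. It is about 1.1 to 1.3 if crossovers at 1.5 to 2 times average risk are also counted as early. These figures rest on assumed inputs and illustrate scale; they do not predict the result. The direction is not fixed, which is a further reason not to call the comparison a test. This should be corrected, but it does not threaten the main result.

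**What to change.** - In 6.5, delete the statement that this comparison tests the hypothesis. In Appendix VII, delete the description of it as the actual hypothesis. State that ITT is the only test.
- In 4.0, 6.5, 8.2 and Appendix VII, describe the treatment-received comparison as non-randomised and descriptive, with no significance test.
- State, in the protocol or by reference to the SAP, which group crossovers, patients who die before angiography and CABG patients fall in.
- Align the sensitivity analysis in 8.3 with the same wording and classification.
- Optional: if an effect of treatment received is wanted, add a supportive estimate in all randomised patients, with randomised arm as the instrument and events counted from randomisation. State that the exclusion restriction is questionable here.

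The cost is wording in the protocol and SAP. The optional estimate adds one model and will have a wider confidence interval than ITT. No data collection, sample size or primary analysis changes.
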